
### Adverse events

Before taking part in the study, potential participants will be screened by researchers over the phone based on inclusion and exclusion criteria of the study protocols. In addition, before being admitted into the study, eligible participants will be provided with an overview of the study procedure, the type of information they will asked to disclose and the level of time commitment the study will require. They will also be informed about the randomisation into either the intervention or control group. While we do not anticipate any parts of the intervention will cause distress, potential participants who feel distress regarding any of the topics will be screened out. When they had been deemed eligible to participate, participants will be provided with age-appropriate full information regarding the intervention. Parents/Carers and children will be given ample time to ask any questions before obtaining written informed consent. It will also be emphasised that they will not be identified in any report and that all their answers will be kept confidential - accessed only by authorised researchers and information obtained will only be used for the purpose of this research. Further, they will be reassured that they are able to choose not to answer questions asked in the study should they find these questions uncomfortable. They will also be reminded they can withdraw from the study at any time without affecting their relationship with the researchers, the University or its affiliates. Interviewers will be instructed to be vigilant about interviewees emotional response to questions asked. Should any of the questions generate an emotional response from interviewees, they will be asked if they want to have a break, postpone or terminate the interview and be referred to appropriate counselling services, a list of which is included in the participant information sheet. As the project's participants are children/families from migrant communities and low socio-economic areas, we will adopt culturally respectful approaches and considerations, but will not compromise the child’s safety and wellbeing. The project will follow the principles outlined in the United Nations' Convention on the Rights of the Child (1989) [60], which has been adopted by the Australian Human Rights Commission. Researchers will also assure children that any data collected will be kept confidential, which is important because of the power imbalance between children and adults. However, if any disclosure of mistreatment or inappropriate behaviour are made during the trial by the parent/carer or child, participants will be informed that the researchers are not equipped to deal with such disclosures and will be provided with contact details to the relevant authorities whose purpose is to deal with such matters. As the trial is being conducted over two states NSW and Victoria, if the need arises participants in NSW will be directed to contact Family and Community Services and participants in Victoria will be advised to contact the Department of Health and Human Services. Kids Helpline materials will also be provided to all field workers to distribute among participants as needed. All bilingual field workers will have Police and Working with Children Checks, will not be alone with a child at any point, and will only complete testing of outcome measures when both a child and their parent/carer is present to avoid any safety concerns.

## Discussion

The Australian Commonwealth and state governments are enthusiastic about trialling and adopting new approaches to addressing child obesity, increasing the likelihood that benefits of the intervention can be translated more widely. This project addresses 3 of the 4 goals in the National Research Priority area of Promoting and Maintaining Good Health: preventing unhealthy weight gain in childhood years (‘preventive healthcare’ and ‘a healthy start to life’) and targeting those who are most vulnerable due to their socio-economic circumstances (‘strengthening Australia’s social and economic fabric’). The study will provide evidence to inform the current National Strategic Framework for Chronic Conditions regarding programs that warrant ongoing support to ensure the most disadvantaged are not left behind in efforts to tackle overweight and obesity. The intervention components have potential for integration into mainstream service delivery, and scalability through health and community services, providing a valuable contribution to the evidence base used in the design of multi-pronged population-based programs, nationally and internationally. The proposed RCT is innovative because it will test the effectiveness of an integrated package of parenting and lifestyle interventions rather than studying the effectiveness of a single intervention (e.g. lifestyle components), providing scientific evidence of the additive effectiveness of a mixed parenting program when combined with a standard lifestyle intervention to prevent unhealthy weight gain and improve the family environment among migrant populations. This study will elucidate methods for engaging socially disadvantaged and culturally diverse groups in parenting programs concerned with child weight status.

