
The primary hypothesis is that improving family functioning among parents or carers of 5 to 11-year-old children from disadvantaged backgrounds will reduce BMIz score immediately following the intervention, and 12-months post-intervention, relative to a control group. The secondary hypotheses (immediately following the intervention and 12-months post-intervention when compared to the control group) include:The percentage of intervention group families functioning poorly and experiencing parenting-related intergenerational conflicts will be decreasedThe percentage of intervention group families eating a family meal together and adopting healthy dietary practices will be increasedAmong parents and their 5 to 11-year-old children, the mean duration of time spent in physical activity will increase, and screen viewing time will decreaseThe percentage of intervention group parents with adequate knowledge regarding healthy lifestyles (healthy food and dietary choices, healthy eating, physical activity, and sedentary behaviours) will increaseThe self-efficacy of these behaviours in children aged 5 to 11 years will be greater in intervention families than the control group following the intervention program

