### Randomisation / group allocation

The trial will use a cluster RCT design with the primary unit of randomisation being postcode. Each of the 92 postcodes within the study areas will be allocated to an intervention or control arm according to a randomisation schedule generated by the trial biostatistician. The allocation ratio between the intervention arm and the control arm is 1:1.

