### Intervention

Consenting participants nested in the postcodes randomised to the intervention arm will receive the intervention as soon as possible after registration. The Strong Families program (the intervention) will be delivered in two stages: A 6-week group program consisting of 6 x 90-minute online sessions covering both healthy lifestyle and parenting modules. The online sessions will be facilitated by bilingual group facilitators with backgrounds in nutrition, dietetics, psychology or social sciences. The modules are designed to provide participants with new knowledge about healthy eating and physical activity (healthy lifestyle modules) and then teach them skills required to effectively implement this knowledge (parenting modules). Then, approximately 3 months after the weekly sessions, participants will attend 2 x 45-minute online booster sessions. The booster sessions are designed to reinforce and enhance the knowledge and skill development acquired in the weekly sessions. These sessions are also intended to allow participants to evaluate the family environment and troubleshoot any challenging areas. Sessions focus on establishing a welcoming and safe environment, and active learning approaches that maximise engagement in knowledge building of healthy habits, making healthy choices, building stronger families and positive family functioning as well as helpful communication strategies that are sensitive to culturally diverse families living in Australia.

The first three (1-3) modules will focus on creating healthy lifestyle choices as a family but particularly in reference to the participating child. This includes concepts such as reducing screen time and sedentary behaviours, making healthy food choices and increasing physical activity. The second three (4-6) modules focus on strengthening the family dynamic through parenting advice and guidance. Specifically, topics discussed include physical, emotional and social development of children, clear and effective boundaries and communication, understanding behaviour and consequences, and managing emotions. The two booster sessions will be revisions of materials previously discussed in the modules and the ensure understanding. Booster A will revise healthy lifestyles and review understanding of healthy food and lifestyle choices. Booster B will review parenting messages covered and provide guidance on maintaining progress in parental decision-making for a stronger family dynamic.

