### Control group

Consenting participants nested in the postcodes randomised to the control arm will not receive the lifestyles and parenting intervention, but rather will receive usual care (self-directed access to and use of parenting and child health services). The control group will form the basis of a comparator group of participants to better understand unhealthy weight gain in children with similar characteristics to the intervention group. All study participants will be invited to an overall presentation and summary of the research findings at the conclusion of the study.

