### Statistical analysis

Data on socio-demographics, anthropometry, general parenting, feeding-related parenting, child’s health and quality of life, physical activity and consumption of healthy foods, parents’ health knowledge and health and household costs will be collected. Child’s anthropometric measurements will be taken at baseline, at completion of the intervention and 12 months after completion of the intervention. Height and weight of the participating child will be used to calculate the BMIz score (primary outcome measure) [57, 58]. Cost per BMIz saved and incremental cost per quality-adjusted life-year gained will also be calculated (Incremental cost per quality-adjusted life-year gained at baseline, end of intervention and 12 months following intervention). Parents will respond to self-administered questionnaire on family functioning, feeding related parenting, physical activity and consumption of healthy foods of the participating child, parents’ health literacy, and family and household costs. The analysis will follow an intention-to-treat approach and with supplementary per protocol analysis. Research data will be analysed with Stata 16 [59]. The statistical analysis will use a modelling approach that aims to capture the profile of the intervention group compared to the control group and while accounting for potential unobserved differences between the intervention and control groups that (if not accounted for) could bias results. The models will evaluate the impact of the interventions over time by testing for an interaction between time and intervention group. This will be followed by multivariable linear models after adjusting for baseline characteristics and other variables (standard demographic variables such as age, sex, income, education, and SEIFA). Subgroup analysis will be undertaken for within-intervention group differences between English speaking and Non-English-speaking groups. Model assumptions will be checked and appropriate adjustments to the analysis made where necessary. A *p*-value <0.05 will be considered statistically significant. The cost-effectiveness analyses will be conducted to determine incremental cost per quality adjusted life year gained by comparing the direct costs and outcomes of behavioural parenting and lifestyle program over usual care from a health care perspective at completion of the intervention and at 12 months post-intervention. The within-trial analysis will adopt a micro-costing approach to calculate the costs of resources used to implement the intervention, including training, staff and travel costs; family or household costs (resources related to food shopping and activities); and health care resources. One of the aims of the project is to undertake economic evaluation to evaluate the effectiveness of the proposed intervention for parents or carers from disadvantaged backgrounds, in preventing unhealthy weight gain in children aged 5 to 11 years living in the same household. This requires data linkage to Medicare funded services and dispensing of subsidised pharmaceuticals to capture total health care expenditure and out-of-pocket costs (Services Australia RMS1190). All analyses will be adjusted for clustering and all participant data will be de-identified prior to analysis.

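### The Discussion promises evidence on the added effect of parenting content, which a two-arm trial of the whole package against usual care cannot identify

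*Protocol article*

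**What the plan says.** In the Discussion, the sentence on why the trial is innovative ends by describing it as "providing scientific evidence of the additive effectiveness of a mixed parenting program when combined with a standard lifestyle intervention". The same sentence opens by saying that the trial tests an integrated package and not a single component.

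The Methods describe the arms as follows:

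- **Intervention:** a "6-week group program consisting of 6 x 90-minute online sessions covering both healthy lifestyle and parenting modules". Modules 1 to 3 are the lifestyle block and modules 4 to 6 the parenting block. Two booster sessions follow, one on each theme.
- **Control:** these families "will not receive the lifestyles and parenting intervention, but rather will receive usual care".
- **Randomisation:** "Each of the 92 postcodes within the study areas will be allocated to an intervention or control arm", and "The allocation ratio between the intervention arm and the control arm is 1:1".
- **Planned test (Statistical analysis):** "testing for an interaction between time and intervention group".

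The primary hypothesis, at the end of the Background, is that "improving family functioning among parents or carers of 5 to 11-year-old children from disadvantaged backgrounds will reduce BMIz score". The sentence goes on to name two times, straight after the intervention and 12 months later, and sets the comparison against a control group. The Abstract lists family functioning among the secondary outcomes.

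**The concern.** To show that parenting content adds something to a standard lifestyle program, a trial needs a group that receives the lifestyle program without the parenting content. This trial has no such group. The Discussion therefore credits the trial with a finding that its design cannot produce.

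What is at stake is how a positive result would be read. The Discussion refers to government interest in adopting new approaches and to the potential of the intervention components for mainstream services. Whether to add parenting sessions to an existing lifestyle program is a decision about one component. If a package effect were reported under the present wording, it would seem to settle that decision when it says nothing randomised about it.

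A smaller mismatch sits in the primary hypothesis. It names improved family functioning as the cause of lower BMIz, but what is randomised and tested is assignment to the whole program.

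**Working it through.** The plan gives no figure for the additive effect, so there is none to reproduce. The check is whether the stated conclusion can be obtained from the stated arms.

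**1. The two quantities.** Write mean BMIz at a given follow-up as M(LP) under lifestyle plus parenting, M(L) under lifestyle alone, and M(0) under usual care.

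- Randomised contrast (Intervention, Control group, Randomisation / group allocation): D = M(LP) − M(0).
- Additive effect of parenting (Discussion): A = M(LP) − M(L).
- Effect of lifestyle alone: B = M(L) − M(0).

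By addition, D = A + B. The trial estimates D. No arm supplies M(L), so there is one equation for two unknowns.

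**2. What that means in numbers.** Take D = −0.15, the size of difference used in the section on sample size determination. The splits below are hypothetical, and the two-arm data could not tell them apart:

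| A (parenting added) | B (lifestyle alone) | D = A + B |
|---|---|---|
| 0 | −0.15 | −0.15 |
| −0.075 | −0.075 | −0.15 |
| −0.15 | 0 | −0.15 |
| +0.05 | −0.20 | −0.15 |

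More families would sharpen D and leave A and B just as undetermined. The 400 per arm in the plan are sized for one difference between two groups.

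**3. Whether another part of the design supplies M(L).**

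- *Timing.* The lifestyle block comes before the parenting block, but measurements are at 0, 10 and 60 weeks. Nothing is measured between the blocks, so not even a non-randomised before-and-after split is available.
- *Separable content.* The blocks overlap. In Table 1, Module 2, a lifestyle module, includes parental feeding practices among its objectives. The Intervention section describes the parenting modules as teaching the skills needed to apply the lifestyle knowledge.
- *Planned analyses.* The main test is time by group. The economic comparison is the program against usual care. The subgroup analysis is by language group. The supplementary per-protocol analysis would at best compare families by attendance, which is not randomised. None targets A.

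**4. The primary hypothesis.** Family functioning is measured after allocation as a secondary outcome. The package also addresses drinks, diet, activity, screen time and sleep. A significant time-by-group term would show that the program changed BMIz. It would not show by randomisation that improved family functioning was the reason. The hypothesis as worded and the planned test are therefore not quite the same statement.

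**The case against.** The strongest reply is that the working parts of the article are already at package level. The Abstract, the end of the Background narrative, the Study design section and the Statistical analysis all speak of the combined program, and the Discussion sentence itself starts that way. No endpoint, sample-size input or decision rule depends on the additive clause, and that it would be misread is a forecast. All of this stands. It limits the weight of the point, but the clause is still an affirmative statement of something the trial cannot provide. An analysis plan not shown could not mend it, since no analysis creates a lifestyle-only comparator.

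A reader might infer something stronger from the primary hypothesis: that the plan promises to prove that better family functioning lowers BMIz. The article does not support that reading. The sentence is a hypothesis and not a promised conclusion. Read to its end, it is set against a control group at two times, and improved family functioning can fairly be taken as loose shorthand for the intervention. Nor would an effect passing through diet and activity contradict it, because the Background places eating and lifestyle practices downstream of the family environment. What remains is that the lifestyle modules could change diet and activity directly, with family functioning unchanged, so the named cause and the tested contrast differ.

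A mediation analysis is commonly left to the analysis plan, and its absence here is not a fault.

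**Conclusion.** The additive claim in the Discussion is wrong as written. The design identifies the effect of the package against usual care and carries no randomised information on how much of it is due to the parenting content. This is a matter of identification and not of degree, so no power or sample-size figure bears on it. It rests only on the arms as the article describes them: both blocks offered to every intervention family, and neither to controls.

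The wording of the primary hypothesis is a lesser mismatch between the stated cause and the tested contrast.

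A reader might also conclude that the two-arm design is itself at fault. It is not: it suits the package-level aim stated elsewhere in the article, and that comparison is untouched.

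**What to change.** 1. In the Discussion, replace the additive-effectiveness clause with: *effectiveness of the integrated parenting and lifestyle package compared with usual care*. This matches the Background aim, the Study design section and the planned test.
2. As a secondary alignment, reword the primary hypothesis along these lines: *the Strong Families program, compared with usual care, will reduce BMIz at the end of the intervention and at 12 months after it*. Family functioning stays where it is, as a secondary outcome.

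Both are text changes. They need no new arm, data, analysis or sample size. The cost is a less ambitious claim: the trial could no longer be presented as evidence for adding parenting content to a lifestyle program.

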## Data Availability

Not applicable.

## Abbreviations

BMI: Body Mass Index
BMIz: BMI-for-age Z-score
IRSD: Index of Relative Socio-Economic Disadvantage
MBS: Medicare Benefits Scheme
POAs: Postal Areas
PBS: Pharmaceutical Benefits Scheme
REDCap: Research Electronic Data Capture
RCT: Randomised Control Trial
SEIFA: Socio-Economic Indexes for Areas
SES: Socio-Economic Status
